### Development process

#### Personalized CBT protocol

Patients in the personalized treatment arm receive personalized treatment for fear of cancer recurrence, depression of cancer-related fatigue. The evidence-based protocols for treating fear of cancer recurrence, depression or cancer-related fatigue were used as a starting point for our personalized version of the treatment [11, 31, 60–62]. The evidence-based protocols were divided into different modules, based on the maintaining factors these modules aim at. This resulted in three to four general modules, essential for every patient, and several optional modules, which will be only provided to patients with these maintaining symptoms. The outcomes of the EMA analyses are used to identify the relevant optional modules for each patient. Table 4 presents the modules per protocol. Experienced cognitive behavioral therapists were asked to provide feedback on the concept protocol, which was processed and led to the definitive treatment protocol. This includes a treatment manual with a detailed description, a format for a personalized treatment plan, and session checklists for each therapy module.

**Table 4 Tab4:** Treatment modules and maintaining factors per protocol

Protocol	Module	Maintaining factor(s)	Mandatory/Optional
*Fear of cancer recurrence (FCR)*			
	Psycho-education	-	Mandatory
	Values, goals, and actions	-	Mandatory
	Attention training	Self-focused attention	Mandatory
	Detached mindfulness and worry postponement	(1) Worry and rumination (2) Attempts to avoid, suppress, or minimize FCR thoughts (3) Intrusive thoughts or images about cancer recurrence	Optional
	Metacognitions	Unhelpful beliefs about the importance, impact and control of worry	Optional
	Threat-monitoring and avoidance	(1) Frequent self-examination (2) Avoidance behaviors	Optional
	Evaluation and relapse prevention plan	-	Mandatory
*Depression*			
	Psycho-education	-	Mandatory
	Goal setting	-	Mandatory
	Activity monitoring	Behavioral inactivity	Optional
	Activity scheduling		
	Behavioral activation		
	Identifying dysfunctional thoughts	Dysfunctional cognitions	Optional
	Changing dysfunctional thoughts (part 1)		
	Changing dysfunctional thoughts (part 2)		
	Relapse prevention	-	Mandatory
*Fatigue*			
	Psycho-education and goal setting	-	Mandatory
	Sleep-wake cycle	Deregulated sleep-wake cycle	Mandatory
	Activity pattern	Deregulation of activity	Mandatory
	Helping cognitions	Dysfunctional cognitions regarding fatigue	Optional
	Fear of cancer recurrence	Fear of cancer recurrence	Optional
	Social interactions	Low social support	Optional
	Coping	Poor coping with cancer and cancer treatment	Optional
	Realizing treatment goals	-	Mandatory

In addition, the secure web-based environment in which patients receive blended or online treatment was developed (Minddistrict; www.minddistrict.com). The format of existing online therapies was adapted for this specific study.

#### Therapists

A master’s degree in Psychology and clinical experience as a therapist are two minimum requirements for participating as a therapist in the study. All participating therapists are trained in working with the treatment protocols (total of 5 training days) and with the online environment. In addition, therapists allocated to the intervention group are separately trained in working with the four dimensions of personalization in the treatment protocol.

During the study, all therapists (in both groups) receive group supervision by experienced clinical psychologists by phone or video-calls every 2 weeks. To avoid contamination, therapists from the intervention group have supervision sessions separate from the therapists from the control group.

### Ecological momentary assessments (EMA)

#### EMA protocol

For the EMA assessments, an existing online electronic diary system is used, designed to monitor patients in their natural environment (http://roqua.nl). Assessments are prompted five times a day for fourteen consecutive days (E0 and E1), after fixed intervals (every 3 h). The exact time points are adapted to patients’ sleep-wake schedule. Patients receive a text message on their smartphone with a link to a questionnaire. They are asked to fill out the questionnaire immediately after the alert. If the patient does not complete the questionnaire within 30 min after the alert, they receive one reminder text message. One hour after the alert, the questionnaire can no longer be accessed. It takes approximately 2 min to complete the questionnaire and it is not possible to skip questions.

#### EMA questionnaires

To determine which questions to include in the electronic diary, the following steps were followed:
Every treatment protocol was divided into multiple modules, based on the maintaining factors these modules aim at. Table 4 presents the individual modules and targeted maintaining factors.EMA items were formulated, based on previous EMA surveys where possible, or on validated, traditional surveys that measured the maintaining factor, in which case the wording of the question was adjusted to reflect the nature of EMA. In case both options were not possible, we formulated the EMA-question ourselves.Three questionnaires were established, one for each treatment protocol, with one or more questions linked to each of the modules and corresponding maintaining factors.The initial set of EMA questions was piloted by a small group of researchers and patients (*n*=4) and adjusted according to the feedback.


#### Back-up questionnaires

It is possible that variables fluctuate too little in some patients, and no valid EMA models can be formed. In this case, the baseline assessment and additional questionnaire(s) are used to identify individual maintaining factors. Patients in both treatment arms fill out the additional questionnaires after the intake. If a patient receives treatment for fear of cancer recurrence, we ask the patient to fill out the 42-item Fear of Cancer Recurrence Inventory (FCRI). Symptoms or issues are rated on a Likert scale from 0 (not at all/never) to 4 (a great deal/all the time). Total scores range from 0 to 168 and a higher score indicates worse fear of cancer recurrence. This questionnaire has sufficient to good reliability and test-retest reliability [69]. The FCRI was also used as primary outcome in the ConquerFear trial [60].

If a patient receives treatment for depressive symptoms, we ask the patient to fill out the 20-item Center for Epidemiological Studies Depression Scale (CES-D). This questionnaire is commonly used in cancer patients and has shown good internal consistency, with alpha coefficients > 0.85 as well as adequate test-retest reliability [70].

If a patient receives treatment for cancer-related fatigue, we ask the patient to fill out additional questionnaires as mentioned in the protocol article of the fatigue intervention [30]. This means the Impact of Event Scale [71], the Modified causal attribution list [72, 73], the Illness management questionnaire [73–75], the Fatigue catastrophizing scale [76], the Self-efficacy scale [73, 77], and the Van Sonderen Social Support Inventory, subscales Interactions (SSLI) and Discrepancies (SSLD) [78]. The psychometric properties of these questionnaires were found to be sufficient.

### Statistical analyses

#### Primary and secondary study parameter(s)

Descriptive statistics will be used to describe baseline characteristics of the experimental and control group and a chi-square test or independent *t*-test will be used to compare baseline characteristics of dropouts and completers in the total sample. Intention to treat analyses will be conducted, i.e., all randomized patients are included and are analyzed in their randomly assigned treatment group. For the intention to treat analyses, linear mixed-model analyses will be performed to evaluate changes in patient functioning from baseline to 6 and 12 months of follow-up (T1 and T2) and differences therein between the experimental group and the control group. Condition, time, and a group × time interaction will be added to the model (as fixed effects) to test for differences between the groups in treatment effects over time. In addition, a random intercept will be used to allow individuals to differ in the level of their outcome variables. Treatment center and manner of referral (self-referral versus referral by treating doctor) will be used as covariates. Based on pooled pre-test standard deviations, effect sizes will be calculated for the estimated differences between T0, T1, and T2 between groups. A significance level of *p*<0.05 is used in all analyses. Since linear mixed model analysis can handle missing observations due to dropout (assuming data are missing at random), imputation of missing values will not be needed. However, patterns of missing data will be explored and predictors of missing data analyzed, especially if these vary by treatment arm. If the primary analysis shows significant effects of personalized CBT, additional sensitivity analyses will be conducted using different assumptions about the value of missing values. Statistical analyses will be performed using SPSS 24.0. The statistical procedure as described above will also be followed for secondary study parameters (fatigue, depressive symptoms, fear of cancer recurrence and quality of life) without the sensitivity analyses. The independent *t*-test will be used to analyze differences between both groups with respect to goal attainment and therapist time.

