### Outcomes

#### Primary outcome

Limitations in daily functioning are measured with the Sickness Impact Profile-8 (SIP-8) [52]. This questionnaire measures limitations in daily functioning across eight domains: sleep and rest, homemaking, mobility, social interactions, ambulation, leisure activities, alertness behavior, and work limitations. The scores across the eight domains are summed to provide one weighted score of limitations in daily functioning (SIP-8 total score). Higher scores reflect higher levels of functional impairment. The SIP yields sufficient levels of reliability and content validity [53]. As severity and type of psychological symptoms in this study will differ among patients (fear of cancer recurrence, depressive symptom, cancer-related fatigue) and mere presence of psychological symptoms is not an indicator for psychological treatment, limitations in daily functioning are the primary outcome of this study. The SIP-8 total score is measured at baseline (T0), end of treatment (T1), and 1 year after start of treatment (T2). The mean difference on the SIP-8 (total score) from T0 to T1 and T2 is compared between both groups.

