### Sample size calculation

As linear mixed models will be used for conducting the primary analyses, it is recommended to base the sample size calculation on a multivariate model [79]. Power analyses for MANOVA were conducted with G*power 3.1.9.2. We want to be able to demonstrate an effect size of 0.25 (partial eta squared) on the primary outcome, while setting the alpha = 0.05 (two tailed) and power = 0.80. With two groups and three measurements each, a sample size of 152 is needed. Taking into account a dropout rate of approximately 20%, a sample size of 190 (95 patients per condition) will be included at baseline.

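### The primary mixed model compares change in SIP-8 without adjusting for baseline, which costs precision, and its random intercept can misstate the standard error of the 12-month contrast

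*Protocol article*

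**What the plan says.** The protocol article, under Primary and secondary study parameter(s), gives the fixed part of the linear mixed model: "Condition, time, and a group × time interaction will be added to the model (as fixed effects". For the random part, "a random intercept will be used to allow individuals to differ in the level of their outcome variables". The adjustment set follows: "Treatment center and manner of referral (self-referral versus referral by treating doctor) will be used as covariates". Baseline SIP-8 is not in it.

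The Primary outcome section defines the comparison: "The mean difference on the SIP-8 (total score) from T0 to T1 and T2 is compared between both groups". T0 is therefore one of three repeated outcomes, and the difference between arms at T0 is estimated rather than set to zero.

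The sections on participant retention and on randomisation say that patients are randomised only after the baseline questionnaires are complete. The article gives no SIP-8 standard deviation, no between-visit correlation and no residual covariance structure.

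**The concern.** Two features of the stated model deserve attention.

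First, T0 is measured before randomisation, so the arms have the same expected T0 score. A model that still estimates a T0 difference and subtracts it carries the full sampling noise of T0 into each contrast. Regressing on T0 removes only the part of T0 that predicts the later score, which gives a smaller variance at no cost in patients. Precision matters here because the comparator is active CBT. The Discussion notes that most earlier comparisons of personalised with standard CBT in non-cancer patients found no difference, and the amendments section reports slow recruitment.

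Second, a random intercept with independent residuals allows patients to differ in level but not in systematic change. It implies one variance at all visits and one correlation for T0-T1, T0-T2 and T1-T2. If the true pattern differs, the model averages over it, and the standard errors of the separate T1 and T2 contrasts can be wrong.

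**Working it through.** **Inputs.** The Sample size calculation gives 152 evaluable patients (76 per arm), two-sided alpha 0.05 and power 0.80. The inflation for dropout checks: 152/0.80 = 190. I take 152 as given. The SD and correlations are not in the article, so I set the SD at T0 to 1 and vary the rest. S_jk is the covariance between visits j and k, and n = 76. The formulas are for complete data.

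**Precision.**
- Change contrast at visit j: (2/n)(S_00 + S_jj - 2S_0j).
- Baseline-adjusted contrast: (2/n)(S_jj - S_0j²/S_00).
- The first minus the second is (2/n)(S_00 - S_0j)²/S_00. This is never negative, so adjustment cannot lose apart from the trivial cost of estimating a slope.
- With equal SDs the ratio of adjusted to change variance is (1 - rho²)/(2 - 2rho) = (1 + rho)/2.

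At rho 0.5 the change SE is √(2/76 × 1) = 0.162 and the adjusted SE is √(2/76 × 0.75) = 0.140. Simulation at N = 152 gave a variance ratio of about 0.76, against 0.75 from the formula.

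| rho (equal SDs) | Variance ratio | SE reduction | Detectable difference in SD at 80% power, change → adjusted | Power for an assumed 0.4 SD, change → adjusted |
|---|---|---|---|---|
| 0.3 | 0.65 | 19% | 0.538 → 0.434 | 55% → 73% |
| 0.5 | 0.75 | 13% | 0.454 → 0.394 | 69% → 81% |
| 0.6 | 0.80 | 11% | 0.406 → 0.364 | 79% → 87% |
| 0.7 | 0.85 | 8% | 0.352 → 0.325 | 89% → 93% |
| 0.8 | 0.90 | 5% | 0.287 → 0.273 | 97% → 98% |

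With SDs 1/1.15/1.25 and correlations 0.55 (T0-T1), 0.40 (T0-T2) and 0.70 (T1-T2):
- T1: change 1 + 1.3225 - 1.265 = 1.0575; adjusted 1.3225 × (1 - 0.3025) = 0.922; ratio 0.87.
- T2: change 1 + 1.5625 - 1.000 = 1.5625; adjusted 1.5625 × (1 - 0.16) = 1.3125; ratio 0.84.

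The saving is then 13% and 16%. If the spread falls after T0 the saving is larger: SDs 1/0.8/0.8 with correlations 0.6/0.5/0.7 give ratios 0.60 and 0.57.

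**Standard error under the random intercept.** The model uses (2/n) × 2 × (mean variance - mean covariance) for both contrasts. The SE ratio is the square root of the model variance over the true variance, and the type I error is 2[1 - Φ(1.96 × SE ratio)]. For correlations 0.60/0.45/0.70 and equal SDs, the mean correlation is 0.583 and the model term is 2 × 0.417 = 0.833. The true T2 term is 2 × 0.55 = 1.10, so the ratio is √(0.833/1.10) = 0.87 and the error 0.088. At T1 the true term is 0.80, the ratio 1.02 and the error 0.045.

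| Correlations T0-T1 / T0-T2 / T1-T2 | T2 SE ratio | T1 error | T2 error | 2-df test |
|---|---|---|---|---|
| 0.6/0.6/0.6 | 1.00 | 0.050 | 0.050 | 0.050 |
| 0.6/0.5/0.6 | 0.93 | 0.041 | 0.068 | 0.051 |
| 0.6/0.5/0.7 | 0.89 | 0.050 | 0.080 | 0.053 |
| 0.6/0.45/0.7 | 0.87 | 0.045 | 0.088 | near 0.05 |
| AR(1), 0.6 | 0.87 | 0.032 | 0.090 | 0.054 |
| AR(1), 0.7 | 0.85 | 0.030 | 0.095 | 0.055 |
| 0.55/0.40/0.70, SDs 1/1.15/1.25 | 0.86 | 0.040 | 0.091 | near 0.05 |
| 0.5/0.5/0.7 | 0.93 | 0.068 | 0.068 | 0.054 |
| 0.5/0.6/0.6 | 1.04 | 0.068 | 0.041 | 0.051 |

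Across all patterns computed, the 2-df test lay between 0.050 and 0.057.

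A small simulation with 95 per arm and 20% lost by T2 (250 runs) gave a mean T2 SE of 0.154 against an empirical SD of 0.171 for AR(1) 0.6, 0.141 against 0.155 for 0.6/0.5/0.7, and 0.141 against 0.136 for equal 0.6. Its T2 rejection rates (0.052, 0.076 and 0.036) have a Monte Carlo error of √(0.05 × 0.95/250) = 0.014, so they neither confirm nor refute the analytic values.

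**The case against.** The difference in change is unbiased under randomisation and is the comparison that the Primary outcome section defines. Not adjusting for baseline is inefficient, not invalid. That stands, and it sets the weight of this point. It does not answer the loss of precision, which is algebraic.

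The size of the gain depends on figures that the article lacks. A flat 25% saving, or 152 patients doing the work of 152/0.75 = 203, needs rho of 0.5 and equal SDs. This also stands, hence the range.

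A reader might infer that the random intercept makes the T2 standard error too small as a matter of fact. The documents do not support that. It requires a T0-T2 correlation below the average of the three, or variances that differ by visit, and neither is reported. In most of the declining patterns T1 is correct or slightly conservative while T2 is not. The group-by-time test with three visits is naturally the 2-df test, which is hardly affected. The per-visit contrasts still matter, because the Primary outcome section refers to T1 and T2 and effect sizes are to be estimated between visits. The section on treatment duration also cites large individual differences in speed of response, which gives a reason to doubt a model without varying change, but no figure.

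The residual structure is unstated, and an analysis plan not shown here could name one. Independent residuals are the usual reading of a random intercept given alone, not a stated choice.

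A reader might also see a mismatch between the analysis and the planning, where "Power analyses for MANOVA were conducted with G*power 3.1.9.2". That is not an error. The section gives the planned mixed models as the reason for a multivariate calculation, and a planning approximation need not share the covariance of the analysis.

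**Conclusion.** The point holds as a recommendation to change the model, not as a fault that invalidates the trial. The loss of precision is certain in direction, because the baseline-adjusted variance is smaller whenever S_0j differs from S_00. Its size is assumption-dependent: a saving of 10% to 35% in variance for rho from 0.8 down to 0.3 with equal SDs, and 13% to 16% in the example with rising SDs. The standard-error point is conditional. Under independent residuals and the assumed declining correlations, the nominal 5% test of the T2 contrast rejects in about 7% to 9.5%. It is exact under equal variances and correlations, and can be slightly conservative otherwise (4.1% for 0.5/0.6/0.6). The overall interaction test stays near its nominal level throughout.

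**What to change.** Either keep T0, T1 and T2 as outcomes but drop the condition main effect so that both arms share one T0 mean, retaining the condition-by-visit terms at T1 and T2, or model T1 and T2 only, with baseline SIP-8 by time as covariate. In both cases replace the random intercept by an unstructured residual covariance (3×3 or 2×2) fitted by REML. Keep treatment centre and manner of referral, and apply the same model to the secondary scales measured at T0, T1 and T2.

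The cost is a line in the analysis section and at most six covariance parameters with about 190 patients. SPSS, the planned software, can fit this. No extra data are needed, since T0 is complete before randomisation. Recruitment was still open under the protocol version described, so the change could be fixed before outcome data are analysed. A further benefit is that the plan relies on data missing at random with about 20% dropout, and likelihood estimates under that assumption are safer when the covariance is not restricted.

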### Aims of the current study

The aim of this study is to investigate if personalized CBT is more efficacious than standard CBT in cancer survivors with moderate to severe fear of cancer recurrence, depressive symptoms, and/or cancer-related fatigue. Primary outcome is limitations in daily functioning. Secondary outcomes are symptoms of fear of cancer recurrence, depression, and cancer-related fatigue; quality of life; goal attainment; drop-out rates; and therapist time needed for treatment delivery. We hypothesize that personalized CBT, in this study defined as an intervention tailored to characteristics and needs of the individual patient, will lead to fewer limitations in daily functioning than standard CBT. We also expect that personalized CBT will lead to less symptoms of fear of cancer recurrence, depression, and cancer-related fatigue; better quality of life; higher goal attainment scores; and lower drop-out rates than standard CBT. Finally, we hypothesize that personalized CBT will not increase the time spent by therapists to deliver the intervention.

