*Goal attainment* is measured with the Goal Attainment Scaling (GAS) procedure. GAS is a method of scoring the extent to which patient’s individual goals for the treatment are achieved. Patients will a priori (at the start of psychological treatment) establish individual criteria for a successful outcome. Each goal is rated on a 5-point scale, with the degree of attainment captured for each goal area. Then, goals are weighted according to their difficulty, and eventually, after end of treatment, goal attainment is evaluated. For details, see Turner-Stokes [58]. This assessment method is included as it concerns a personalized outcome measurement, in which treatment is evaluated based on outcomes specifically relevant and important to the individual patient. Goal attainment is measured at the end of treatment. At this time point, the mean score is compared between both groups.

Therapists register their *time spent on each patient during treatment*. This includes preparation time, registration time in the patient data files (summarizing session), the number of sessions, and time needed to formulate e-consults or feedback in Internet-based or blended therapy. Therapist time is assessed after end of treatment. At this time point, the average time is compared between both groups.

*Drop-out rates* are collected for both treatment arms. In this study, a drop-out is defined as patients who discontinue the intervention before the planned end of the intervention. Patients’ reasons for discontinuing the intervention or declining to fill out follow-up questionnaires will be collected. Drop-out rates at T1 and T2 are compared between both groups.

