## Discussion

To our knowledge, this is the first study comparing the efficacy of personalized CBT to standard CBT in cancer survivors with moderate to severe fear of cancer recurrence, depressive symptoms, and/or cancer-related fatigue. The study has several innovative characteristics.

The first is the head-to-head comparison between personalized CBT and standard CBT. There has been a repeated call for personalized psychological treatments for cancer patients [15–17]. Multiple studies have applied personalization in cognitive behavioral therapy (CBT) for cancer survivors or patients with cancer [18–28]. However, to the best of our knowledge, only one study compared personalized CBT to standard CBT [19]. In the other studies, personalized CBT was compared to a wait list group or another intervention such as a psycho-education. To determine if and the extent to which personalized CBT has added value over standard CBT in cancer survivors, more studies with a head-to-head comparison are needed. Our study enables a direct comparison.

A second innovative characteristic of this study is the personalization of psychological treatment on various dimensions. Other studies, in which the efficacy of personalized CBT was compared to standard CBT in non-cancer patients, mostly found no significant difference between the two treatment forms. Researchers suggested that insufficient contrast between the two interventions could have partly accounted for the lack of difference [80–82]. Therefore, we aimed to expand the contrast in this study by delivering a package of personalization measures. Should these measures eventually not lead to a difference between treatment arms, the expectations of the added value of personalized psychological treatments should perhaps be reconsidered. However, if personalized CBT appears to be more efficacious than standard CBT, it will remain unclear which personalization measure or combination of personalization measures explains the difference. Further research could then explore the extent to which each personalization measure adds value to personalized CBT. For example, the MOST design could be used to further optimize the intervention [83]. For clarity, we decided to personalize CBT on multiple dimensions to maximize the contrast between personalized CBT and standard CBT.

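### Sensitivity analyses for missing SIP-8 data are planned only if personalized CBT shows a significant effect, so a null result is not tested against departures from missing at random

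*Protocol article*

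**What the plan says.** All of the following is in the protocol article.

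- **Primary model** (Statistical analyses, Primary and secondary study parameter(s)). A linear mixed model of SIP-8 at T0, T1 and T2 includes all randomized patients. Missing follow-up is left to the model: "assuming data are missing at random), imputation of missing values will not be needed".
- **What is done whatever the result** (same section). "patterns of missing data will be explored and predictors of missing data analyzed, especially if these vary by treatment arm". Baseline characteristics of drop-outs and completers are also compared in the total sample.
- **What depends on the result** (same section). "If the primary analysis shows significant effects of personalized CBT, additional sensitivity analyses will be conducted", under other assumptions about the missing values.
- **Secondary outcomes** (same section). The same model is used for these: "fatigue, depressive symptoms, fear of cancer recurrence and quality of life) without the sensitivity analyses".
- **Expected drop-out** (Aims of the current study). Personalized CBT is hypothesised to give "higher goal attainment scores; and lower drop-out rates than standard CBT". Under Secondary outcomes, "a drop-out is defined as patients who discontinue the intervention before the planned end of the intervention". The Sample size calculation allows about 20% overall, with no split by arm.
- **Use of a null result** (Discussion). "Should these measures eventually not lead to a difference between treatment arms, the expectations of the added value" of personalized treatment should, the sentence goes on, perhaps be reconsidered.

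**The concern.** Missing at random cannot be verified from the observed data. The usual protection is to repeat the analysis under stated departures from it and see whether the conclusion changes. Here that step is taken only when the primary analysis shows a significant effect of personalized CBT. A false positive caused by informative missingness would be examined. A real benefit masked by it would not.

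One-sided checking of this kind is easier to accept when only a positive result will be interpreted. In this trial the authors also say what they might conclude from no difference, and that conclusion rests on the same untestable assumption. A significant result in favour of standard CBT is in a similar position, because the wording of the condition does not clearly cover it.

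**Working it through.** **The plan's own figure.** The only stated number that bears on missing data is the inflation for drop-out: 152 / (1 − 0.20) = 190, or 95 per arm. It reproduces exactly. It corresponds to 190 − 152 = 38 patients lost overall and says nothing about how they divide between arms.

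**Bias formula.** Higher SIP-8 is worse. Let m_S and m_P be the shares missing in the standard and personalized arms. Let δ_S and δ_P be how much worse, in SD, the missing patients are than the model predicts. Each arm's mean then looks too good by m × δ, so

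estimated benefit = true benefit − (m_S·δ_S − m_P·δ_P).

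**Illustration.** The shares and shifts below are assumptions. A split of 25% and 15% of 95 gives 23.75 + 14.25 = 38 patients, which agrees with the planned 20% overall.

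| m_S | m_P | δ_S | δ_P | Change in estimated benefit |
|---|---|---|---|---|
| 0.25 | 0.15 | 0.5 | 0.5 | −(0.125 − 0.075) = −0.05 SD |
| 0.25 | 0.15 | 1.0 | 1.0 | −(0.25 − 0.15) = −0.10 SD |
| 0.20 | 0.20 | 1.0 | 1.0 | 0 |
| 0.15 | 0.25 | 1.0 | 1.0 | +0.10 SD |
| 0.25 | 0.15 | −1.0 | −1.0 | +0.10 SD |
| 0.20 | 0.20 | 1.0 | 0.5 | −(0.20 − 0.10) = −0.10 SD |

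Rows 4 and 5 show that the direction reverses if either the imbalance or the shift reverses. Row 6 shows that equal missingness does not remove the bias when the shift differs by arm.

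**Effect on the test.** A simulation of the mixed-model analysis used 95 patients per arm, three visits, within-person correlation 0.5, a true benefit of 0.40 SD at T1 and T2, a two-degree-of-freedom group-by-time test and 600 replicates per row. Missing patients lacked both follow-ups. The benefit, correlation, shares and shifts are all assumed. The Monte Carlo standard error of a power figure is at most √(0.5 × 0.5 / 600) = 0.02.

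| Missing, standard / personalized | δ (both arms) | Mean estimate (SD) | Power |
|---|---|---|---|
| 20% / 20% | 0 | 0.40 | 0.77 |
| 20% / 20% | 1.0 | 0.41 | 0.79 |
| 25% / 15% | 1.0 | 0.30 | 0.49 |
| 30% / 10% | 0 | 0.40 | 0.74 |
| 30% / 10% | 0.5 | 0.29 | 0.49 |
| 30% / 10% | 1.0 | 0.21 | 0.26 |
| 10% / 30% | 1.0 | 0.60 | 0.98 |

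The estimates agree with the formula (for example 0.40 − 0.10 = 0.30 in row 3). The last row would usually be significant, so the plan would examine it. Rows 3, 5 and 6 would be non-significant in about half or more of trials, and the plan would then run no sensitivity analysis. With no true effect, 30% / 10% missing and δ = 1.0, the mean estimate was 0.20 SD in favour of standard CBT, and the test rejected in 22% of replicates.

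**The case against.** Several points on the other side stand.

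- **A reader might infer that the protocol predicts more missing SIP-8 data in the standard arm.** It does not. Its hypothesis concerns drop-out, defined as stopping the intervention, and such patients can still complete questionnaires. T1 and T2 are timed from intake, and non-responders are contacted after one week. The protocol does connect the two: its analysis section speaks of observations missing because of dropout. Unequal missingness is therefore possible, but it is not stated.
- **A reader might infer that a null result would go wholly unchecked.** That is also too strong. The exploration of missing-data patterns, with attention to differences by arm, is unconditional and could reveal an imbalance. It cannot show how much the treatment estimate would change if the missing values departed from the model's predictions.
- **Patients who leave need not be doing worse.** The background on treatment duration describes ending treatment once improvement is sufficient. If those lost were doing better than predicted, the bias would reverse.
- **The condition is prespecified and can only weaken a positive claim.** That is a recognisable conservative choice in a superiority trial. It gives no protection to a null result.
- **The remark about a null result is hedged.** It is a comment in the Discussion and not a decision rule.
- **Method details belong in an analysis plan that is not shown.** This is true of the choice of technique. The condition itself is written in the protocol.

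**Conclusion.** The point holds in a limited form. The protocol makes its only planned analyses under other missing-value assumptions depend on a significant effect of personalized CBT. A null result therefore gets no such analysis, and one favouring standard CBT is not clearly covered.

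Under an assumed 25% versus 15% missing and a shift of 0.5 to 1.0 SD in both arms, the bias toward zero is 0.05 to 0.10 SD. The protocol supports neither the split nor the shift, and other assumptions give no bias or the opposite bias. The figure shows what the omitted analysis would explore; it does not forecast this trial.

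It is tempting to express the bias as a share of the planned effect. The documents do not support that. The Sample size calculation gives 0.25 labelled partial eta squared, which does not convert to a difference in SD without further assumptions about within-person correlation and how the effect is spread over visits.

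The change is worth making because it is cheap and the null result may be interpreted. It does not call the primary analysis into question.

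**What to change.** Delete the condition. State that a missing-not-at-random sensitivity analysis of SIP-8, for example delta-adjusted or tipping-point, will be run and reported whatever the direction or significance of the primary result, with the shift varied separately in each arm. Predictors of missingness found in the exploration already planned can go into any imputation model used for it.

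The cost is one sentence and a few hours of analysis. Sample size, alpha and the primary model do not change. Recruitment was still open in the version reviewed, so at that stage the change could be made before results were known.
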